#### Primary aim 1: effectiveness

##### Effectiveness

We define *effectiveness* metrics as those that assess the impact of the ICBHSS initiative using annual community household surveys, routine programmatic data, and the health facility assessments. The community-level primary outcome by district uses under-five mortality rates as well as the secondary outcomes of neonatal, under-one, under-two, and maternal mortality rates. We will additionally evaluate quality of care parameters focusing on timeliness of child healthcare through promptitude of treatment reception following illness diagnosis and health facility readiness scores. Lastly, we will assess equity through secondary analyses of under-five mortality by household wealth quintiles, maternal education levels, and distance from the nearest health facility.

*Primary outcome: under-five mortality rates*. We will calculate under-five mortality rates from all births reported by respondents using a standard birth/death history table. We will calculate under-five mortality rates and compare the risk of death before age five across surveys with the Cox proportional hazards regression using intervention exposure as the explanatory variable. Children still alive and under age five at the time of survey will be right censored.

*Secondary outcomes: neonatal, under-one, and under-two mortality rates*. We will calculate the neonatal, under-one, and under-two mortality rates from all births reported by respondents using the same methods described above adjusted for 28 days, 1 year, and 2 years.

*Secondary outcome: maternal mortality*. We will calculate an exploratory maternal mortality analysis based on sisterhood reports [57, 58].

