#### Community-based household surveys

Females 15–49 years of age who reside in a selected household within the study catchment area are included. Participants 15–17 years of age will only be included if they have been/are currently pregnant and have a waiver of parental permission. Households will be randomly selected each year using a systematic population-weighted sampling methodology. If there is more than one eligible respondent in the household, one will be randomly selected based on a Kish selection grid [54]. All participants will have the opportunity to decline participation during the informed consent process.

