### Sample size determination

This study is powered to detect a change by cluster in under-five mortality per 1000 live births. A sample size of 7600 participants will provide 80% power to detect an estimated 30% reduction or greater of under-five mortality from the estimated baseline of 70 per 1000 live births, with an alpha of 0.05, intracluster correlation of 0.005, 20% non-response rate, and estimated 0.5 children under five per participant [9, 55]. Effect size is a conservative estimate based on past pilot experience (ClinicalTrials.gov Identifier: NCT03773913).

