		Children under five mortality rate	Community-based household survey	Using a standard birth/death history table, calculate under-five mortality rates, and compare risk of death before age five across surveys with the Cox proportional hazards regression using survey year as the explanatory variable. Children still alive and under age five at the time of survey will be right censored.
		*Secondary outcomes*		
		Neonatal mortality rate	Community-based household survey	The neonatal mortality rates from all births reported by respondents in the 5 years prior to the survey using the same methods described for under-five mortality, adjusted for 28 days.
		Children under one mortality rate	Community-based household survey	The under-one mortality rates from all births reported by respondents in the 5 years prior to the survey using the same methods described for under-five, adjusted for 1 year.
		Children under two mortality rate	Community-based household survey	The under-two mortality rates from all births reported by respondents in the 5 years prior to the survey using the same methods described for under-five, adjusted for 2 years.
		Maternal mortality rate	Community-based household survey	Exploratory maternal mortality analysis based on the sisterhood reports [57, 58].
		Quality of care parameters		
		Timeliness/promptitude of child care for malaria	Routine programmatic data	Proportion of children under five reported febrile and the proportion who received effective antimalarial treatment within 24 h of symptom onset.
		Timeliness/promptitude of child care for pneumonia	Routine programmatic data	Proportion of children under five reported with cough and the proportion of those children who received an effective pneumonia treatment within 24 h of symptom onset.
		Timeliness/promptitude of child care for diarrhea	Routine programmatic data	Proportion of children under five reported with diarrhea and the proportion of those children who received an effective treatment for diarrheal disease within 24 h of symptom onset.
		CHW technical competence	Routine programmatic data	Proportion of IH CHWs who adhere to evidence-based protocols for iCCM and maternal health.
		Facility clinical staff technical competence	Routine programmatic data	Proportion of facility clinical staff who adhere to evidence-based protocols for iCCM and maternal health.

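### Births entering the mortality outcomes: text and Table 4 disagree for three secondary outcomes, and the primary outcome has no recall window in either place

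*Protocol article*

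**What the plan says.** **Primary outcome.** The Effectiveness section (Primary aim 1) states: "We will calculate under-five mortality rates from all births reported by respondents using a standard birth/death history table". The Table 4 row for under-five mortality also refers to a birth/death history table and gives no window.

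**Secondary child mortality outcomes, text.** "We will calculate the neonatal, under-one, and under-two mortality rates from all births reported by respondents using the same methods described above", with the age limit changed to 28 days, 1 year and 2 years.

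**The same outcomes, Table 4.** "The neonatal mortality rates from all births reported by respondents in the 5 years prior to the survey"; "The under-one mortality rates from all births reported by respondents in the 5 years prior to the survey"; "The under-two mortality rates from all births reported by respondents in the 5 years prior to the survey". The table adds that these follow the method given for under-five mortality.

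**Who reports.** Inclusion criteria, Community-based household surveys: "Females 15–49 years of age who reside in a selected household within the study catchment area are included".

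**Sample size.** The calculation uses an "estimated 0.5 children under five per participant".

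**Model.** The text compares risk across surveys by Cox regression on intervention exposure. Table 4 names survey year as the explanatory variable. Surveys are at baseline and at 12, 24, 36 and 48 months, with one district starting each year.

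**The concern.** Two instructions for the same three outcomes cannot both be followed. For the primary outcome, the only stated rule admits births as far back as a woman of 49 can report, about 34 years, in a trial that lasts four.

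Older births add almost nothing about the intervention, and the harm they do depends on how exposure is coded. If every child reported in a post-rollout survey counts as exposed, decades of pre-rollout deaths are labelled exposed and the effect is diluted. If child-time is split at the start date, the same deaths fall into the unexposed group. If mortality was also falling and the model has no calendar-time term, that group looks worse for reasons unrelated to the intervention. The Background section says child mortality in Togo fell over recent decades, so the second route cannot be dismissed.

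The choice of births therefore helps decide the primary estimate, and it should be settled before data are analysed.

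**Working it through.** **1. Passages side by side.**

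| Outcome | Effectiveness text | Table 4 |
|---|---|---|
| Under-five (primary) | all reported births | no window given |
| Neonatal, under-one, under-two | all reported births | births in the last 5 years |

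**2. What the sample size implies.** An illustrative projection assumes total fertility of 4.3–6.4, age-structure growth of 2–4.5% a year, 55% of under-five deaths in the first year and constant past mortality. None of these is in the article. It gives 0.59–0.91 births per woman in the last 5 years and 1.84–3.29 over a lifetime. The plan's 0.5 children under five per participant is close to the first range and far from the second.

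The plan's total of 7600 could not be reproduced. Two-sided, 70 against 49 per 1000 needs 1991 children per arm. That is 3982 in total, 3982/0.5 = 7964 participants, and 7964/0.8 = 9955 after non-response, before any allowance for the intracluster correlation. Sidedness and whether 7600 is per survey are not stated, so nothing here rests on that figure.

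**3. How old the births are.** In the same projection, 68–72% of births in an unrestricted history are more than 5 years before the survey, 43–48% more than 10 years and 12–14% more than 20 years.

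Can such births be exposed at all? The longest exposure at any survey is 48 months. A child born 61 months before the final survey in the first district was 61 − 48 = 13 months old at the start, so some exposed time at ages one to four is possible. A child born more than 5 + 4 = 9 years before any survey can have none. Older births therefore carry little exposed time, mostly after the first year of life, and beyond 9 years none.

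**4. Dilution if exposure is coded by survey round.** Let s be the share of deaths in a post-rollout survey that truly occur after rollout. With a true ratio of 0.70, the apparent ratio is 1 − 0.30 × s. For 2% growth:

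| Years since rollout | s, all births | Apparent ratio | s, 5-year births | Apparent ratio |
|---|---|---|---|---|
| 1 | 0.06 | 0.982 | 0.26 | 0.923 |
| 2 | 0.12 | 0.965 | 0.49 | 0.853 |
| 3 | 0.18 | 0.947 | 0.70 | 0.791 |
| 4 | 0.23 | 0.931 | 0.87 | 0.739 |

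At 4.5% growth the four-year ratios are 0.919 and 0.738. A true 30% reduction thus appears as about 2–8% with all births and 8–26% with 5-year births.

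**5. Averaged over the rollout.** Assume starts directly after the surveys at 0, 12, 24 and 36 months. The ten post-rollout district-surveys then have 1, 2, 3 and 4 years of exposure in the ratio 4:3:2:1.

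- All births: s = (4×0.06 + 3×0.12 + 2×0.18 + 0.23)/10 = 0.119; ratio 1 − 0.30×0.119 = 0.964.
- 5-year births: s = (4×0.26 + 3×0.49 + 2×0.70 + 0.87)/10 = 0.478; ratio 1 − 0.30×0.478 = 0.857.

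The visible reduction falls from 30% to 14.3% through survey-round coding, and from 14.3% to 3.6% through the all-births rule. Two separate models gave 0.96–0.97 with all births and 0.82–0.86 with 5-year births.

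More births do not make up for this. All births supply 2.2/0.61 = 3.6 times as many per woman. Signal relative to noise, ignoring clustering, is then (0.036 × √3.6)/0.143 ≈ 0.48 of that with the 5-year window.

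**6. If exposure is coded by child-time.** With no secular trend, both windows recover 0.70. With no intervention effect, no calendar-time term and an assumed past decline of 2% to 4% a year, the ratio drifts to 0.94–0.89 with 5-year births and 0.78–0.59 with all births. The drift comes from the missing time term, and the longer window magnifies it.

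**The case against.** The best defence is that Table 4 is there to clarify the text: it repeats the phrase about reported births, adds the 5-year limit, and ties the secondary outcomes to the under-five method. On that reading a 5-year window was meant throughout, and the 0.5 children per woman supports it. The questionnaire is not shown and may itself limit recall. This stands as a plausible account of intent, and it bars the inference that lifetime histories will certainly enter the primary analysis. It does not remove the conflict, since the primary outcome is given no window anywhere. The censoring rule, limited to children alive and still under five, also suggests that older children are in the data. The further inference that under-five and under-one rates will come from different cohorts holds only if the primary outcome truly has no window.

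A reader might also infer that the trial is set to manufacture a benefit of 22–41%. The documents do not support that. It needs child-time coding, no adjustment for time, and a steady decline over decades at an assumed rate. Comparing across surveys, with survey year in Table 4, points rather to coding by survey. Whether time is adjusted for is unclear: Table 4 refers to mixed-effects models as if described for the primary outcome, the Reach section adjusts such models for time, and the Discussion says the analysis plan mitigates temporal trends.

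Finally, part of the dilution is a separate problem of survey-level exposure coding, which no birth window cures. That stands, and step 5 shows the split.

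**Conclusion.** The point holds. The text and Table 4 give different birth cohorts for neonatal, under-one and under-two mortality. The primary outcome's only stated rule is all births, which does not match the unit used in the sample size.

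If that rule is followed and exposure is coded by survey round, a true 30% reduction would be seen as about 2–8%, against 8–26% with 5-year births. Averaged over the assumed rollout, that is about 4% against 14%. These figures rest on assumed fertility, age structure and age pattern of death, and on constant past mortality; they show size only. Under child-time coding the bias could favour the intervention, but its size cannot be fixed from the article. Under child-time coding with proper time adjustment, old births would do little harm and add little information. It is not established that decades of older deaths will enter the analysis, only that the wording allows it.

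**What to change.** State one recent window for all child mortality outcomes, the primary included, in both the Effectiveness text and Table 4. Table 4's births in the 5 years before the survey is the simplest choice, and the dilution figures above were computed for it. Child-time in the 60 months before the survey, with late entry for children born earlier, is an acceptable alternative; its gain was not computed here. Keep all births as a sensitivity analysis only.

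A window does not remove pre-rollout child-time from the early post-rollout surveys. The same edit should therefore tie exposure to each district's start date, adjust the Cox model for calendar time, and use one explanatory variable in text and table.

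The cost is a few sentences and no new data. Older births leave the primary analysis. Under the 5-year birth window this includes some exposed time at ages one to four from children born 5–9 years before the later surveys, which the 60-month child-time option would keep where it falls within those 60 months.

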## Background

While Togo has observed reductions in child mortality over the last few decades, accelerated progress is needed to achieve Sustainable Development Goal (SDG) goal 3.2, to reduce neonatal mortality to 12 per 1000 live births and under-five mortality to 25 per 1000 live births [1, 2]. Most recent subnational estimates from 2013-2014 show that the infant mortality rate in the northern region of Kara is 62 per 1000 live births and the under-five mortality rate is 130 per 1000 live births, compared to national rates of 49 and 88 per 1000 live births, respectively [3]. The principal causes of under-five deaths in Togo are diseases with effective and low-cost interventions and treatments, including malaria, acute lower respiratory infections, and diarrheal diseases [3]. Despite Togo’s national plan for the integrated management of childhood illness (IMCI), a policy on integrated community case management (iCCM), and the Expanded Program on Immunization (EPI), Togo has not observed comparable reductions in child mortality as compared to neighboring peer nations including Burkina Faso, Ghana, and Guinea [4]. Furthermore, Togo’s Ministry of Health (MoH) reports that national utilization rates of public sector health facilities are less than 30%, even though 62% of the population lives within 5 km of these facilities [5, 6].

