#### Stepped-wedge cluster randomized control trial

This pragmatic design leverages the sequential or staggered rollout of the ICBHSS model and will facilitate an assessment of effectiveness as well as implementation strategy through coverage and adoption metrics by comparing geographically organized clusters [50, 51]. It includes four clusters that organize intervention health facilities by district: Bassar, Binah, Dankpen, and Kéran. The ICBHSS cluster initiation order will be randomized annually with four steps, as it was independently determined by the IH programs team that baseline health needs were similar in each cluster. Community-based household surveys adapted from Demographic and Health Survey (DHS) modules previously implemented in Togo [3] and focusing on demographic, maternal, and child health data will be conducted in each cluster at baseline, 12, 24, 36, and 48 months.

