#### Primary aim 2: implementation strategy

##### Reach

We define *reach* metrics as the proportion of target population that gained access to the ICBHSS initiative services using the annual community household surveys. We will assess the implementation strategy through individual-level ICBHSS participation with community-level (vis-à-vis CHWs) and facility-level health service utilization using health service coverage estimates and early service access for child health. We will use a mixed-effects generalized linear model to compare pre-intervention to post-intervention proportions for each *reach* metric while adjusting for clustering at the facility and district level and time and allowing for district-level estimates to be random effects. Our primary analysis will not include adjustment for individual-level characteristics, as each district will serve as its own control.

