## Discussion

We have described our rationale, study design, and implementation strategy details regarding this pragmatic type II hybrid design to serve as a model for those interested in pragmatic implementation studies that allow for continuous intervention improvement.

This study design includes several limitations, including limitations with any real-world pragmatic stepped-wedge trial. There are concerns related to confounding, bias, and temporal trends that may limit the validity of our findings. We used a modest effect size, a cluster randomization, and an analysis plan to mitigate these limitations. There are contextual factors that may be challenging to delineate that influence our primary outcomes. We attempted to minimize this at baseline through site selection.

In spite of these limitations, this study will enable a rigorous evaluation in a real-world setting that measures effectiveness and implementation strategy, while also contributing to knowledge generation to inform and complement national health strategies. A one-size-fits-all approach for evaluation does not work for the implementation of multiple interventions and corresponding strategies, particularly in real-world settings. We intend to provide an effective intervention accompanied by an implementation roadmap that includes enabling and non-enabling factors. Through this directed scientific inquiry and mixed-methods evaluation, we aim to contribute to knowledge and foster partnerships that improve quality and access to community health systems in Togo and beyond.

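### The primary mortality analysis is stated as two incompatible single-variable Cox models, and neither separates the programme effect from calendar time or includes district

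*Protocol article*

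**What the plan says.** The protocol article describes the primary analysis of under-five mortality in three places that do not agree.

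- **Primary aim 1, Effectiveness, primary outcome:** the plan is to "compare the risk of death before age five across surveys with the Cox proportional hazards regression using intervention exposure as the explanatory variable". No time, district, stratum, frailty or clustering term is named.
- **Table 4, under-five mortality row:** the same Cox analysis "with the Cox proportional hazards regression using survey year as the explanatory variable". This has calendar time but no intervention term and no district.
- **Table 4, the two care-cascade rows under Adoption:** these point to mixed-effects generalized linear models supposedly set out for the primary effectiveness outcome. Neither the Effectiveness section nor the mortality row describes such a model.

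For reach, by contrast, the article gives the terms a stepped wedge needs, comparing pre- and post-intervention proportions "while adjusting for clustering at the facility and district level and time and allowing for district-level estimates to be random effects". The Adoption section carries this over to its own measures.

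The Discussion concedes that "There are concerns related to confounding, bias, and temporal trends that may limit the validity of our findings" and names the analysis plan among the mitigations. The Background opens with "While Togo has observed reductions in child mortality over the last few decades".

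**The concern.** In a stepped wedge, exposure accumulates with calendar time by design. Randomising the order of districts decides which district is early. It cannot make exposed and unexposed observation times alike. A model with exposure alone therefore credits the programme with any background change in mortality, and one with survey year alone does so even more directly. Because secondary measures get the time and clustering terms and the primary outcome does not, an analyst following the article could report a benefit that the programme did not produce. An analyst could also choose between two different primary results.

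**Working it through.** **The plan's own figure.** The sample size section gives 7600 participants for 80% power to detect a 30% reduction from 70 per 1000, with alpha 0.05, intracluster correlation 0.005, 20% non-response and 0.5 children per participant.

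- Children: 7600 × 0.8 × 0.5 = 3040. Read as per survey round (an assumption), this is 760 per district-survey.
- Hussey-Hughes variance (fixed periods, random district), I = 4, T = 5, U = 10, W = V = 30.
- Total variance 0.07 × 0.93 = 0.0651; τ² = 0.005 × 0.0651 = 0.0003255; s² = 0.995 × 0.0651/760 = 0.0000852.
- Var = I·s²(s² + Tτ²) / [(IU − W)s² + (U² + ITU − TW − IV)τ²] = 4 × 0.0000852 × 0.001713 / (10 × 0.0000852 + 30 × 0.0003255) = 0.0000550, so SE = 0.00742.
- Power = Φ(0.021/0.00742 − 1.96) = Φ(0.87) = 80.8%.

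So 7600 and 80% reproduce under a model with period and district terms, if 7600 is per survey. If 7600 is the total over five surveys (152 children per cell), the same formula gives 26%.

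**Calendar gap.** I assume no district is exposed at the baseline survey and one more at each later survey (four districts, five surveys, a new district every 12 months). Number the surveys 0 to 4.

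- Exposed cells: (1×1 + 2×2 + 3×3 + 4×4)/10 = 3.0.
- Unexposed cells: (4×0 + 3×1 + 2×2 + 1×3)/10 = 1.0.
- The gap is two years.

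**Exposure-only model, true hazard ratio 1.00.** Let mortality fall by a fraction d a year, r = 1 − d, with equal child-time per cell, each survey's deaths assigned to its own period, and exposure coded by survey status. The apparent hazard ratio is (r + 2r² + 3r³ + 4r⁴)/(4 + 3r + 2r² + r³), which is very nearly r².

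| Assumed decline a year | Apparent hazard ratio |
|---|---|
| 1% | 0.98 |
| 2% | 0.96 |
| 3% | 0.94 |
| 4% | 0.92 |
| 5% | 0.90 |

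**Survey-year model (Table 4).** With no programme effect, the last survey against the first gives r⁴: 0.99⁴ = 0.96 to 0.95⁴ = 0.81. Every survey covers all four districts, so district mix is balanced, but nothing separates trend from programme.

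**District.** The share of exposed cells minus the share of unexposed cells, by order of start, is +0.3, +0.1, −0.1, −0.3. These sum to zero, so over random orders the expected shift is nil. The spread is not. The planning intracluster correlation implies a between-district SD of √0.0003255 = 0.018, or 0.018/0.07 = 0.26 relative to the baseline rate. The SD of the log hazard ratio is √0.20 × 0.258 = 0.115, a 95% range of about 0.80 to 1.25 from district differences alone (0.79 to 1.26 by simulation).

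**False-positive rate of the exposure-only model.** At a 3% decline the log hazard ratio shifts by −0.061.

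- 15,200 children (5 × 3040): about 1002 deaths, nominal SE 2/√1002 = 0.063, true SD √(0.063² + 0.115²) = 0.131. Two-sided rejection is about 40%. The trend alone gives 16% and district spread alone 35%.
- 3040 children in all: about 200 deaths, SE 0.141, true SD 0.182. Rejection is about 15%. The trend alone gives 7% and district spread alone 13%.

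In simulation, adding period and district terms returned a hazard ratio of about 1.00 and about 5% error. The simulated data had a trend common to all districts, which is what that model assumes.

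**The case against.** The strongest reply is that a journal article condenses a fuller plan. Naming the explanatory variable of interest does not say that nothing else is in the model, and the Discussion points to an analysis plan. The cross-reference in Table 4 suggests a mixed model was once intended, so this may be a drafting slip rather than a decision against adjustment. That is fair as to intent, and a reader should not infer that adjustment was considered and rejected. It does not remove the point. The article states a primary model, states a different one in Table 4 and points to a third that is absent, while spelling out the missing terms for reach. That is contradiction, not brevity.

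Three stronger readings are tempting and are not supported.

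- **A spurious reduction of up to 41%.** Coding exposure by child-time over all reported births gives apparent hazard ratios of about 0.78 to 0.59 at declines of 2% to 4%. The Effectiveness section does refer to all births. But the lowest value needs an assumed 4% decline, child-time coding that the article does not state, and assumed uniform maternal ages and constant fertility. It shows that the bias can be larger, not what it is.
- **District differences create a false benefit.** If the first district started at 90 and the last at 50 per 1000 (assumed, the other two equal), the contrast shifts by 0.3 × 90 − 0.3 × 50 = +12 per 1000, which would hide a benefit. Either sign is possible.
- **Table 3 refutes the statement that "baseline health needs were similar in each cluster".** Catchment-weighted utilisation is 42.9% in Bassar, 39.5% in Binah and 14.9% in Dankpen, with Kéran unknown. Utilisation is not health need; low use may reflect access or cost.

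The evidence for a decline is also limited. The Background statement is national and long-run, it adds that progress lags neighbouring countries, and the Abstract says morbidity and mortality stayed high over the past decade, especially in the north. No annual rate or trend for Kara is given.

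**Conclusion.** The point stands. The primary model is stated inconsistently, and neither explicit form can separate the programme from calendar time. Under the exposure-only form the bias is towards benefit whenever mortality is falling. By survey status it is about 0.98 to 0.90 for an assumed decline of 1% to 5% a year, which is real but modest beside the target hazard ratio of about 0.70. It is larger if exposure is coded by child-time over all births. The direction follows from the design once a decline is granted; the size rests on the assumed rate. Omitting district is a different fault: no fixed direction, but chance confounding and understated standard errors with four clusters. At the planning intracluster correlation this contributes more to the false-positive rate than a 3% trend does.

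**What to change.** Reconcile the Effectiveness section, the under-five mortality row of Table 4 and the two cross-references in the adoption rows, so that one primary model is stated everywhere. A suitable form is a Cox model on the age scale with a time-varying intervention indicator, calendar-period terms, and district as stratum or fixed effect. State how exposure is assigned to child-time and which births enter. Name an inference method suited to four clusters. A permutation test over the 4! = 24 possible orders, for example, cannot give a p-value below 1/24 = 0.042, so this choice needs thought in advance.

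The cost is analysis wording only; no new data are needed. The interval will be wider: on the planning inputs the adjusted SE of 0.00742 compares with √(0.0651/760 × (1/10 + 1/10)) = 0.00414 without adjustment, a ratio of about 1.8. That is the precision the design supports, and the stated 80% power is consistent with it if 7600 is per survey round. The sample size text should say whether it is.

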Following this successful preliminary pilot phase and considering the need, IH was requested by the MoH to expand the ICBHSS model to additional sites starting in 2018. In collaboration with the MoH and technical partners, IH is replicating the ICBHSS model in 21 distinct rural health facilities in four additional districts. In collaboration with MoH partners, IH’s ICBHSS program team designed an implementation strategy for this expansion to enhance adoption, implementation, and sustainability of the model [34–36]. This strategy enables a rollout to a new district every 12 months, and is based on pilot experience, local contextual factors as well as budgetary and feasibility considerations. As part of this expansion launched in 2018, IH and MoH partners designed a stepped-wedge randomized trial to enable a rigorous assessment of intervention effectiveness and implementation strategies to inform national policy.

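### The primary Cox model has two different explanatory variables and no rule to split child follow-up at rollout; followed as written, it counts pre-rollout deaths in post-rollout surveys and dilutes a 30% effect

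*Protocol article*

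**What the plan says.** In the protocol article, the Effectiveness section under Primary aim 1 describes the primary analysis in three steps:

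- Births: "We will calculate under-five mortality rates from all births reported by respondents using a standard birth/death history table". No look-back window is given.
- Model: "compare the risk of death before age five across surveys with the Cox proportional hazards regression using intervention exposure as the explanatory variable".
- Censoring: "Children still alive and under age five at the time of survey will be right censored".

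Table 4 describes the same outcome and the same Cox model, but gives survey year as the explanatory variable. It sets a five-year look-back for the neonatal, under-one and under-two rates and none for the primary outcome.

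On timing, the section on context and the ICBHSS model says "This strategy enables a rollout to a new district every 12 months". The stepped-wedge section says that household surveys "will be conducted in each cluster at baseline, 12, 24, 36, and 48 months". Respondents are women aged 15 to 49 (Inclusion criteria).

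**The concern.** A birth history is retrospective. When a woman is interviewed 12 months after her district's rollout, a child of hers born four years earlier has lived three years without the programme and one with it. A child who died before rollout was never exposed.

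Survey year takes one value per child record, so it cannot separate these periods. It is also the same for all districts at a given survey, whether or not they have started. A comparison between surveys that classes the whole record by the district's status at interview has the same weakness: deaths before rollout are charged to the intervention. The bias is towards no effect, on the trial's primary effectiveness outcome. It grows with the length of the birth history, and the primary outcome sets no limit on that length.

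**Working it through.** **The plan's own figure.** The sample size section states: "A sample size of 7600 participants will provide 80% power", for 0.070 against 0.049, with "alpha of 0.05, intracluster correlation of 0.005, 20% non-response rate, and estimated 0.5 children under five per participant".

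- 7600 × 0.8 × 0.5 = 3040 children.
- Two-sided two-proportion formula: n = [1.96√(2 × 0.0595 × 0.9405) + 0.8416√(0.0651 + 0.0466)]² / 0.021² = 1991 per group, or 3982 children. With no allowance for clustering this is 3982 / 0.5 / 0.8 = 9955 women.
- A Hussey–Hughes stepped-wedge calculation gives about 30–34% power if 7600 is the total over five surveys and 86–89% if it is per survey. The article does not say which.

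No variant that uses all the stated inputs gave 7600 at 80% power. That is a separate matter and does not enter the dilution below.

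**Inputs for the dilution check.**

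- From the article: four districts, 12 months between rollouts, surveys at 0, 12, 24, 36 and 48 months, 70 deaths per 1000, a 30% reduction.
- Assumed: true hazard ratio (HR) 0.70 from rollout; no secular trend; cumulative deaths of 25 per 1000 by 1 month, 45 by 12 months and 70 by 60 months; births spread evenly over 5 to 30 years, or over 30 years with a 7% yearly decline going back; first rollout at month 0 or month 12 (the Table 2 timeline is a figure that is not shown).

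**Step 1: time since rollout.** With the first rollout at month 0 there are 4 + 3 + 2 + 1 = 10 exposed district-surveys, at 12, 24, 36 and 48 months since rollout in the ratio 4:3:2:1. The mean is (48 + 72 + 72 + 48)/10 = 24 months.

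**Step 2: child-time, ignoring mortality.**

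- Five-year births: the post-rollout share at E months is 1 − ((60 − E)/60)², that is 0.36, 0.64, 0.84 and 0.96. Weighted: (1.44 + 1.92 + 1.68 + 0.96)/10 = 0.60, so 40% is pre-rollout. With the first rollout at month 12 the weights are 3:2:1 and the share is (1.08 + 1.28 + 0.84)/6 = 0.53, so 47% is pre-rollout.
- Births over L months, for L of 120 or more: the mean post-rollout share is 24/(L − 30). For 10 years this is 24/90 = 0.27; for 20 years, 24/210 = 0.11. So 73% and 89% are pre-rollout.

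**Step 3: deaths and apparent HR.** Monthly hazards are −ln(0.975) = 0.0253 in month 0, 0.00188 in months 1–11 and 0.00055 in months 12–59, multiplied by 0.70 after rollout. The age-stratified estimate is HR = Σ(D₁T₀/T) / Σ(D₀T₁/T), first with whole records classed by the district's status at survey, then with child-time split at rollout.

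| Births used | Pre-rollout deaths in exposed surveys | Pre-rollout child-time | HR, whole record | HR, first rollout month 12 | HR, split |
|---|---|---|---|---|---|
| Last 5 years | 62% | 40% | 0.86 | 0.88 | 0.70 |
| 10 years | 83% | 73% | 0.93 | 0.94 | 0.70 |
| 15 years | 89% | 84% | 0.96 | 0.96 | 0.70 |
| 20 years | 92% | 89% | 0.97 | 0.97 | 0.70 |
| 30 years, declining | 89% | 85% | 0.96 | 0.96 | 0.70 |

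Thirty years of evenly spread births gives 0.98. For five-year births with the first rollout at month 12, 68% of deaths in exposed surveys are pre-rollout. Other age patterns moved the five-year figure (first rollout at month 0) to between 0.82 and 0.86.

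**Step 4: adjustment for district and survey.** The five-year HR becomes 0.95 (first rollout month 0) or 0.91 (month 12). Five-year histories from successive annual surveys share four years, so little within-district contrast is left.

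**Step 5: information after splitting.** Post-rollout child-time carries about 23% of expected deaths (five-year births) or 5–11% (longer histories). Schoenfeld's formula, (1.96 + 0.8416)² / [p(1 − p)(ln 0.70)²], gives 247 deaths at p = 0.5. It gives about 343 at the five-year share and about 610–1220 at the longer ones, before any allowance for clustering or period.

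**The case against.** The strongest reply is that the article never says follow-up is left unsplit. Intervention exposure in the Effectiveness text could be coded as time-varying, and such coding is commonly left to an analysis plan that is not shown here. This stands as far as it goes: a reader might infer that the plan has chosen the wrong coding, and the Effectiveness text alone does not support that. It does not dispose of the point, because Table 4 fixes a variable that rules out splitting, and both places frame the comparison as one between surveys.

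A second reply is that a five-year window may be intended, since the sample size assumes 0.5 children under five per participant. That too is fair. Under that window a reader might infer that most child-time in exposed surveys is pre-rollout, or that the effect all but vanishes. Neither holds for the unadjusted analysis: only 40–47% of child-time is pre-rollout, and about half the effect remains. Near-disappearance applies to all births, which is what the text says, or after adjustment for district and survey, which the article states for the reach models but not for this Cox model.

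Third, a reader might conclude that an effective programme would probably be reported as ineffective. A design with exactly 247 deaths split equally would have 22% power at HR 0.86 and 4–8% at 0.93–0.97. But the number of deaths the trial will observe cannot be derived while it is unclear whether 7600 is a total or per survey.

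Finally, the censoring rule is correct and is needed under any version of the analysis.

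**Conclusion.** The concern holds in this form: the article gives two incompatible explanatory variables for its primary model and no rule for child-time before rollout, and one of the two necessarily mixes pre- and post-rollout deaths. If whole records are classed by survey, a true 30% reduction appears as about 12–14% with five-year births and about 2–7% with births going back 10 to 30 years. The direction of the bias is the same under every birth window tested, and splitting at rollout removes it in all of them. The exact size rests on the assumed age pattern of death, birth distribution, rollout timing and absence of a secular trend, none of which the visible text supplies. This should be settled before the primary analysis.

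**What to change.** - Reconcile Table 4 with the Effectiveness text so that one explanatory variable is named for the primary Cox model.
- Define intervention exposure as time-varying: split each child's follow-up at the district's rollout date, using the dates of birth and death in the birth/death history. Time and deaths before that date count as unexposed, and those after it as exposed. Include district and calendar-time terms.
- State a look-back window for the primary outcome.
- Restate the power on post-rollout child-time, and say whether 7600 is a total or per survey.
- Keep right-censoring at survey.

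The cost is some analysis programming and a text correction, provided the birth/death history records dates as such tables normally do. The downside is that the stated power may become less favourable, because exposed child-time carries a minority of the expected deaths.
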